#### Data management

Participants will be coded in the randomization process and all paper versions of coding and collected data will be stored in fireproof cabinets. Digital data will be stored in secure coded files by JH.

#### Confidentiality

Due to Swedish law (the Swedish Privacy Protection Law), data will not be available for, or shared with, other researchers.

### Statistical analysis and power calculation

To detect a difference of 6 mmol/mol in HbA1c (SD ± 10), which is a clinically relevant difference and based on previous studies [43], it is necessary to include at least 44 participants in each group (power 80% and alpha 0.05). Taking a dropout rate of 12% into consideration, a total of 100 patients will be included in the study. All analyses will be conducted on an intention-to-treat basis, which also can allow evaluation of the feasibility of the method. Differences between the groups will be analysed with un-paired Student’s *t* test with a 95% confidence interval, or non-parametric Mann-Whitney test. *P* < 0.05 will be considered as statistically significant. Multiple linear regression analysis will be used to examine which variables contribute the most to glycaemic control at 6 and 12 months.

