## Methods/design

### Study design and setting

This is a parallel-group multicentre randomized controlled trial with an allocation ratio of 1:1 and a superiority framework. The study will be conducted at the Unit for Youth at Sachs’ Children and Youth Hospital (aged 15–20 years old) and at the outpatient diabetes clinic at Ersta Hospital (aged 18–20 years old) in Stockholm, Sweden. A flow chart of the study is presented in Fig. 1. The GSD-Y method was tested in six patients at our clinic before the study started and the questionnaires that we use are all validated and have been used by our research group in previous studies.

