### Intervention

Individuals in the intervention group will receive seven individual GSD-Y visits (of 1–1.5 h) with a facilitator (either a diabetes nurse or a physician) over 3 to 6 months. The facilitator is educated in the GSD-Y method. The GSD-Y method includes that the participant works with structured reflection sheets. By filling in reflection sheets before each visit and using their own words and drawings, participants systematically explore and express their own experiences and difficulties with diabetes in daily life. In addition, if the participant is under 18 years of age, her parents will be offered one individual visit and one visit together with the participant according to the GSD-Y method. The topics for the different visits are presented in Table 1. The first reflection sheet will be sent or given to the participants before the first visit. For subsequent visits, the reflection sheet for the next meeting will be distributed at that visit and completed before the next visit. In the dialogue between the participant and the facilitator, the facilitator uses different communication methods including mirroring, active listening, and value-clarifying responses. Those participants who have taken part in the first five GSD-Y visits will be considered to have completed the education. Visits are booked in consultation with each participant and, if a participant misses out of a visit, she will be offered another appointment provided she wants to continue with the study.

**Table 1 Tab1:** Overview of reflections sheets

Visit 1	Your life with diabetes from the beginning to now
	Written invitation to work together in a new way
	Two ways of looking at glycosylated haemoglobin (HbA1c)
	Agreement on things to work on
Visit 2	Your life with diabetes from the beginning to now
	Important events and periods in your life
	What do you find difficult at present living with your diabetes?
	Your plans for changing your way of life
Visit 3	Values and opportunities
	Unfinished sentences: needs, values, experiences, and opportunities
	Individual visits for parents are offered
Visit 4	Diabetes in your life
	A picture or expression describing your life with diabetes
	Room for diabetes in your life
	Shared responsibility between adolescent and parent for diabetes in daily life
	Common name for difficulty in your life with diabetes
	Agreement on things to work on until next visit
Visit 5	Problem identification and problem solving
	Current problem solving

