### Measures and data collection

Data will be collected shortly before randomization and at 6 and 12 months. At 6 and 12 months the questionnaires will be sent by mail to participants to fill in and to send back to JH in pre-addressed envelopes. If they fail to respond, the participants will be contacted by telephone. Baseline data will be used to describe characteristics of participants who discontinue.

The primary outcome is HbA1c at 12 months after the randomization. Secondary outcomes are self-management and psychosocial parameters based on questionnaires.

Data to be collected from participants includes: 1) HbA1c (DCA 2000), height, weight, and insulin dose per kilo body weight; 2) self-management (daily self-monitoring of blood glucose, downloaded data on self-monitoring of blood glucose (SMBG)/CGM/FGM); 3) data on socioeconomic background; 4) other diseases/disorders; and 5) number of planned and completed visits; 6) psychosocial self-efficacy (Swedish Diabetes Empowerment Scale (Swe-DES 23) [36]).

Data to be collected from participants and, if participant < 18 years, from parents includes: 1) treatment satisfaction (Diabetes Treatment Satisfaction Scale (DTSQ) Teen and Parent [37]); 2) perceived health and QoL (Check your health [7, 38], Disabkids [39]); and 3) diabetes-related family conflicts (Diabetes Family Conflict Scale (DFCS) [40]).

In this study masked assessors are not used. The primary outcome is a solid biochemical measure and the secondary outcomes include measurements on ordinal scales from validated questionnaires, and they should not be sensible to external influence. The other secondary outcomes (height, weight, insulin dose, SMBG/FGM/CGM) are registered by nurses not involved in the study.

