#### Primary outcome

The primary outcome is HbA1c at 12 months after the randomization. HbA1c will be measured in connection with clinical visits right before randomization and at 6 and 12 months after. We define the baseline HbA1c as the mean HbA1c at randomization and 6 months prior to randomization in order to capture a representative value.

HbA1c levels will be assessed from capillary blood tests and analysed in the DCA Vantage apparatus (Siemens Healthcare Diagnostics, Upplands Väsby, Sweden).

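### The intention-to-treat label rests on a test that uses only observed 12-month HbA1c, about 88 of 100 participants as planned, and leaves the baseline and 6-month values unused

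*Protocol article*

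**What the plan says.** All references are to the protocol article.

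- **Statistical analysis and power calculation.** The analysis principle is "All analyses will be conducted on an intention-to-treat basis". Group differences are to be tested with an unpaired Student's t test or a Mann-Whitney test. Multiple linear regression is mentioned, but its purpose is to find which variables contribute most to glycaemic control at 6 and 12 months, not to estimate the treatment effect. The sample size is "To detect a difference of 6 mmol/mol in HbA1c (SD ± 10") with "at least 44 participants in each group (power 80% and alpha 0.05"), and then "Taking a dropout rate of 12% into consideration, a total of 100 patients will be included in the study".
- **Primary outcome.** The outcome is HbA1c at 12 months. "HbA1c will be measured in connection with clinical visits right before randomization and at 6 and 12 months after". Baseline is defined as the mean of the value at randomisation and the value 6 months earlier.
- **Intervention.** A participant who misses a GSD-Y visit is rebooked on a condition: "she will be offered another appointment provided she wants to continue with the study". Attending the first five visits counts as completing the education. No analysis set is built on that definition.
- **Measures and data collection.** "Baseline data will be used to describe characteristics of participants who discontinue". The article says nothing else about how discontinuers are handled.

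**The concern.** Intention-to-treat means that every randomised participant counts in her allocated arm. A two-sample test on a single time point cannot deliver that when some values at that time point are missing. A participant without a 12-month HbA1c drops out of the test, even if her baseline and 6-month values are on file. The article itself expects up to 12 of 100 to be in that position.

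Two things are at stake. One is precision: HbA1c usually correlates with its own earlier values, and the plan goes to the trouble of averaging two readings for baseline, yet the named test uses neither that baseline nor the 6-month value. The other is attrition bias. Only the intervention arm has seven sessions of 1 to 1.5 hours with reflection sheets, and the Discussion says late cancellations are common. If losses are more frequent in that arm and concentrated among those with poor control, the observed comparison favours GSD-Y. The rebooking condition in the Intervention section adds to the worry, because it speaks of continuing with the study where continuing with the visits may be meant.

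**Working it through.** **Inputs from the article:** difference 6 mmol/mol, SD 10, alpha 0.05, power 80%, 44 per group, dropout 12%, 100 in total, allocation 1:1.

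**Assumptions that are not in the article:** a two-sided test; SD 10 refers to the 12-month value; a correlation between baseline and 12-month HbA1c of 0.5 to 0.7; the split and the difference of those lost, as stated in step 4.

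**1. The plan's own figures.**
n per group = 2 × (1.960 + 0.842)² × 10² / 6² = 43.6, rounded up to 44. This agrees with the article. (A one-sided test would need 35, so two-sided is the reading that fits. The exact t-test solution is 44.6.)
Total = 88 / (1 − 0.12) = 100. This also agrees. Conversely, 100 × 0.88 = 88, so the plan counts on 88 participants with a 12-month value.

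**2. Power of the stated t test** (standardised difference 6/10 = 0.6).
- 44 per arm: 79.5%.
- 50 per arm: 84.4%, if the full 6 mmol/mol effect holds in everyone.
- 50 per arm, with 12% of the intervention arm getting no effect: the difference is 6 × 0.88 = 5.28 and power is 74.3%.

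Recovering all 12-month values therefore does not guarantee a gain in power. Its value is mainly protection against bias.

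**3. Power with baseline adjustment, 44 per arm.**
Residual SD = 10 × √(1 − r²).

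| r (assumed) | Residual SD | 6 / residual SD | Power |
|---|---|---|---|
| 0 | 10.00 | 0.600 | 79.5% |
| 0.5 | 8.66 | 0.693 | 89.5% |
| 0.7 | 7.14 | 0.840 | 97.4% |

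So adjustment gives about 90% to 97% with the same participants. Averaging two baseline readings tends to raise r. Selecting on HbA1c at entry (values below 52 mmol/mol are excluded) tends to lower it.

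**4. Attrition bias of the observed comparison.**
If a share m/50 of an arm is lost and those lost run D mmol/mol above those observed, the observed mean is too low by (m/50) × D. The bias in the difference is (m₁/50 − m₀/50) × D.
- Balanced and alike, 6 lost in each arm: (6/50 − 6/50) × D = 0.
- 9 lost in the intervention arm, 3 in control: (9/50 − 3/50) × D = 0.12 × D. For D = 4, 8 and 12 this is 0.48, 0.96 and 1.44 mmol/mol in favour of GSD-Y.
- Relative to the 6 mmol/mol target: 0.48/6 = 8% up to 1.44/6 = 24%.

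**The case against.** The strongest reply is that the article nowhere restricts the primary analysis to completers, and this is correct. A reader might infer a completer comparison from three places, and none of them supports it.

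- **Dropout allowance.** Going from 88 to 100 is ordinary planning against lost information. It removes nobody from the analysis and does not contradict intention-to-treat.
- **Rebooking.** The sentence makes a new appointment depend on staying in the study. It does not make follow-up depend on attending visits. It leaves unclear what happens to someone who stops GSD-Y but is content to be followed, and it states no withdrawal rule.
- **Discontinuers.** The article says their baseline data will be described. It does not say that this is all that happens to their data.

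HbA1c is taken at clinical visits, within ongoing care, so a participant who stops GSD-Y can still have a 12-month value and is then tested in her allocated arm. Available-case is therefore the right description.

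Two further points stand. A rule for missing values is commonly left to the full protocol or SAP, neither of which is shown, so its absence alone is no fault. The legend of the flow chart lists ANOVA, but the figure is not shown, so further planned analysis may exist. And the bias figures depend entirely on an assumed split and difference. If most 12-month values turn out to be in the clinic record and are used, the bias largely disappears.

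What the reply does not remove is the choice that the article does fix: a single-time-point, unadjusted test as the between-group analysis, beside an intention-to-treat promise and HbA1c measurements that the test leaves unused.

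**Conclusion.** The point holds as a weakness in the chosen analysis, of should-fix weight. The sample-size arithmetic is correct. The stated primary test yields an unadjusted available-case comparison of about 88 of 100 randomised participants, to which the intention-to-treat label only partly applies.

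The more certain loss is precision: 79.5% power at 44 per arm, against about 90% to 97% with baseline adjustment, given a correlation of 0.5 to 0.7 and SD 10 for the 12-month value. The bias is conditional: none under balanced and like dropout, about 0.5 to 1.4 mmol/mol under the 9-to-3 scenario. The documents do not show that GSD-Y discontinuers will be excluded, nor that available HbA1c values will be thrown away.

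**What to change.** 1. **Primary analysis.** Replace the two-sample test with a repeated-measures model of HbA1c at 6 and 12 months, adjusted for baseline HbA1c, with participants analysed as randomised and the 12-month contrast as primary. This keeps participants who have a 6-month but no 12-month value. A sensitivity analysis that shifts missing intervention-arm values upward is a reasonable addition.
2. **Follow-up.** State that stopping GSD-Y visits is not withdrawal from the study. For every randomised participant who has not withdrawn consent for data use, take the routine clinic HbA1c nearest 12 months from the patient record. The article already plans to draw visit counts from that record. Reword the rebooking sentence so that continuing the visits and continuing the study are separate.

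Cost: a slightly more elaborate model, changes of wording in the protocol and the consent form, and record look-up for about 12 participants. No additional participants or measurements are needed. The article gives January 2020 as the approximate end of recruitment, and both changes are best made before outcome data are examined.

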**Fig. 1 Fig1:**
[figure not shown]
Flow chart for GSD-Y versus standard care. *ANOVA* analysis of variance, *CGM* continuous glucose monitoring, *DFCS* Diabetes Family Conflict Scale, *DTSQ* Diabetes Treatment Satisfaction Questionnaire, *FGM* flash glucose monitoring, *GSD*-*Y* guided self-determination-young, *HbA1c* glycosylated haemoglobin, *SMBG* self-monitoring of blood glucose, *Swe*-*DES 23* Swedish Diabetes Empowerment Scale

This paper follows the Standard Protocol Items Recommendations for Interventional Trials (SPIRIT) guidelines for intervention trials. The SPIRIT checklist and figure are included as Additional file 1 and Fig. 2.

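### The primary comparison of 12-month HbA1c gives the trial's own baseline HbA1c no role; adjusting for it would add precision at almost no cost

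*Protocol article*

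**What the plan says.** The Primary outcome section fixes the endpoint as a level at one time point: "The primary outcome is HbA1c at 12 months after the randomization". The same section takes care over the baseline: "We define the baseline HbA1c as the mean HbA1c at randomization and 6 months prior to randomization in order to capture a representative value".

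Under Statistical analysis and power calculation, group differences are to be analysed with an unpaired Student's t "test with a 95% confidence interval, or non-parametric Mann-Whitney test". No covariate is named for this comparison. The sizing statement in that section reads "To detect a difference of 6 mmol/mol in HbA1c (SD ± 10"), and leads to 44 per group at 80% power and alpha 0.05, then to 100 in total after 12% dropout. It does not say whether the SD belongs to the 12-month level or to the change.

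The section closes with a regression: "Multiple linear regression analysis will be used to examine which variables contribute the most to glycaemic control at 6 and 12 months". Its covariates are not listed, and it is not described as the estimate of the treatment effect.

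**The concern.** The baseline is averaged over two readings so that it is representative, yet the comparison that decides the trial has no stated place for it. HbA1c at 12 months can be expected to correlate with HbA1c at entry in the same patient. The part of the outcome variance that baseline explains then stays in the error term, and the confidence interval is wider than the collected data require.

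The Randomization section describes blocks of two and no stratification on HbA1c, so the design does not balance baseline HbA1c either. In the one trial that is run, a chance difference at baseline carries over in part to the unadjusted 12-month difference. At stake are several points of power and a more stable primary estimate, in a trial of 100 patients with no margin beyond the dropout allowance.

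**Working it through.** **Inputs from the protocol article** (Statistical analysis and power calculation): difference 6 mmol/mol, SD 10, alpha 0.05, power 80%, 44 per group, 12% dropout, 100 in total. Sidedness is not stated; two-sided reproduces the figure, whereas one-sided would give 35 per group.

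**Inputs assumed:** r, the correlation between baseline and 12-month HbA1c, over the range 0.3 to 0.7; SD 10 read as the SD of the 12-month level; and, for step 4 only, a baseline SD of 10.

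**1. The plan's own figure.** n per group = 2 × (1.960 + 0.842)² × 10² / 6² = 43.6, rounded up to 44. Total = 88 / 0.88 = 100. Both stated figures reproduce. Power at 44 per group is 80.4% by the normal approximation and 79.5% by the noncentral t distribution.

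**2. Power with baseline as covariate.** Residual SD = 10 × √(1 − r²). Power is for 44 per group and difference 6, noncentral t. The half-width is that of the 95% interval, 1.96 × SD × √(2/44).

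| r (assumed) | Residual SD | Power | 95% CI half-width (mmol/mol) |
|---|---|---|---|
| unadjusted | 10.00 | 79.5% | 4.18 |
| 0.3 | 9.54 | 83.1% | 3.99 |
| 0.4 | 9.17 | 85.9% | 3.83 |
| 0.5 | 8.66 | 89.5% | 3.62 |
| 0.6 | 8.00 | 93.6% | 3.34 |
| 0.7 | 7.14 | 97.4% | 2.98 |

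**3. Check by simulation** (5,000 trials per setting, 44 per group, normal data). At r = 0.5 the t test had 79.3% power and ANCOVA 89.1%; at r = 0.7, 79.4% and 97.2%. With no true effect, the t test rejected in 4.5% and 5.1% of trials and ANCOVA in 4.6% and 4.7%. Both hold their level.

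**4. Chance imbalance.** With baseline SD 10, the standard error of the baseline difference is 10 × √(2/44) = 2.13 mmol/mol. An imbalance above 3 mmol/mol in either direction lies beyond 3 / 2.13 = 1.41 standard errors, a chance of about 16%. The shift in the unadjusted estimate is slope × imbalance. With equal SDs the slope is r, so at r = 0.6 the shift is 0.6 × 3 = 1.8 mmol/mol, or 1.8 / 6 = 30% of the target difference.

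The shift for an imbalance of one standard error does not depend on the assumed baseline SD. The slope is r × SD(12 months) / SD(baseline), and the standard error is SD(baseline) × √(2/44), so SD(baseline) cancels. The result is r × 2.13, which is 0.85 mmol/mol at r = 0.4 and 1.49 at r = 0.7 (14% and 25% of 6).

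**5. If SD 10 is instead the SD of change** (equal variances at both times). The level SD is 10 / √(2(1 − r)): 10 at r = 0.5 and 12.9 at r = 0.7. By the normal approximation, the unadjusted test of the level then has 80% and 59% power, and ANCOVA 90% and 86%. The direction is the same.

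**The case against.** The strongest reply is that nothing stated is wrong. The sample size reproduces, the unadjusted t test keeps its type I error, and its interval already allows for chance imbalance over repeated randomizations. All of that stands. A reader might infer that the trial is underpowered or its primary test biased; the document's figures do not support this. Imbalance affects the estimate in a single trial, not the long-run error rate, and only the fraction r of it carries over when the SDs are equal.

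A second reply is that the regression sentence already supplies an adjusted analysis. It does concern HbA1c at 12 months, but its stated aim is to find which variables contribute most. It is not named as the treatment comparison, so it does not fill the gap.

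A third is that the t test might be applied to changes from baseline. The statistical section does not say, but the endpoint is defined as the 12-month level. Even on changes, ANCOVA would be more precise: with equal variances the ratio of error variances is (1 − r²) / (2(1 − r)) = (1 + r)/2, which is 0.8 at r = 0.6.

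Several stronger readings should be set aside:

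- **The test is picked after the data are seen.** The article says nothing on timing. The sentence covers all group differences, and Measures and data collection describes questionnaire outcomes on ordinal scales, so Mann-Whitney may be meant for those. Even taking the better of the two tests gave a simulated type I error of only 5.0% to 6.1%.
- **ANOVA is a conflicting third method.** The Fig. 1 legend expands the abbreviation ("analysis of variance"), but the figure is not shown, so its use cannot be judged.
- **Site and age must be adjusted for.** One centre recruits only older participants ("at the outpatient diabetes clinic at Ersta Hospital (aged 18–20 years old"), but no stratification is described and no prognostic strength is given. This adjustment is a preference, as is a linear model for the questionnaire scores.

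**Conclusion.** The point holds as a matter of efficiency. The protocol names an unadjusted comparison for its primary outcome and gives its carefully defined baseline no role in it. On the stated inputs, adjustment would raise power from 79.5% to between 83% and 97% for r from 0.3 to 0.7, and narrow the 95% interval half-width from 4.2 mmol/mol to between 4.0 and 3.0.

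These gains rest on an assumed r and on reading SD 10 as the SD of the 12-month level. The entry limit on HbA1c (52 mmol/mol or above) may lower r, and averaging two baseline readings may raise it. The 3 mmol/mol imbalance example also rests on a baseline SD of 10; restricted entry and averaging both tend to make the true value smaller.

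This is not a detail deferred to an unseen analysis plan, because the article itself names the tests. The change is worth making, but the trial's validity does not depend on it.

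**What to change.** In Statistical analysis and power calculation, name one primary analysis: a linear regression (ANCOVA) of 12-month HbA1c on randomized arm and baseline HbA1c as defined under Primary outcome, reporting the adjusted mean difference with its 95% confidence interval. Keep the t test or Mann-Whitney test of 12-month HbA1c as a sensitivity analysis. State that the explanatory regression is separate from this treatment comparison.

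The sample size can stay at 100; the gain in precision is a margin against the uncertain SD and correlation. The cost is one degree of freedom and a change of wording. No new measurements or patients are needed, since both baseline readings are already part of the plan. The change should be recorded before the 12-month results are compared by arm.
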